## ABSTRACT

Exercise-based cardiac rehabilitation (CR) is a non-drug procedure already clinically incorporated with grade AI recommendation for post-acute myocardial infarction (AMI) patients in the outpatient phase. However, such evidence derives from studies in later phases after the cardiac event. CR in the in-hospital phase and early to the event has grown in the last decade, but its efficacy and safety during the procedure need to be clarified with more robust methodological designs. Thus, this study aims to analyze the effectiveness of a CR protocol based on physical exercises on physical fitness, morphology, and cardiac function, in addition to the cardiohemodynamic safety of inpatients with recent AMI. A controlled and randomized clinical trial will be carried out at the University Hospital Onofre Lopes (HUOL) with a CR protocol based on early physical exercise (>8 hours of clinical stability) of patients with AMI with success in percutaneous coronary intervention (PCI). After randomization, patients will be grouped into GI and CG (intervention and control group). GI will be submitted to a standard low-intensity CR protocol and CG to usual care and mobilization guidelines. Subjects in both groups will undergo the same functional assessments, maximal and submaximal (cardiopulmonary and 30s sit-to-stand tests), cardiac nuclear magnetic resonance, and analysis of heart rate variability. Safety scores and cardiohemodynamic events during rehabilitation will be analyzed. It is expected to observe, at the end of the study, a positive effect of in-hospital CR on cardiac structure and function and its clinical repercussions on the increase of physical fitness, allowing a greater understanding of exercise prescription variables and their physiological responses to predict more therapeutic strategies. efficient and early interventions during the in-hospital rehabilitation process in patients with AMI.

**Keywords:** Early cardiac rehabilitation; physical performance; exercise dose; acute myocardial infarction.

## LISTA DE ABREVIATURAS

|               |                                                                     |
|---------------|---------------------------------------------------------------------|
| AACVPR | American Association of Cardiovascular and Pulmonary Rehabilitation |
| CF     | Cardiorespiratory fitness                                           |
| ACSM   | American College of Sports in Medicine                              |
| AHA    | American Heart Association                                          |
| CVD    | Cardiovascular Disease                                              |
| COPD   | Chronic Obstructive Pulmonary Disease                               |
| EF     | Ejection Fraction                                                   |
| HUOL   | Hospital Universitário Onofre Lopes                                 |
| ICP    | Percutaneous Coronary Intervention                                  |
| MIA    | Myocardial Infarction Acute                                         |
| MET    | Metabolic Equivalent of Task                                        |
| CR     | Cardiac Rehabilitation                                              |
| RCR    | Reverse Cardiac Remodeling                                          |
| NRM    | Nuclear Resonance Magnetic                                          |
| MR     | Myocardial Revascularization                                        |
| ACS    | Acute Coronary Syndrome                                             |
| CPET   | Cardiopulmonary Exercise Test                                       |
| CST    | CST Chair Sit-Stand Test                                            |
| 6mWT   | 6 Minute Walk Test                                                  |
| HRV    | Heart Rate Variability                                              |

## INTRODUCTION

### 1.0 Acute Coronary Syndrome (ACS) and Myocardial Infarction Acute (MIA)

Acute coronary syndrome (ACS) occurs due to a sudden reduction or absence of blood flow in the coronary arteries, resulting, therefore, in a perfusion deficit of the cardiac tissue. The clinical presentation of the syndrome can be broad and vary from the typical symptom of acute chest discomfort to electrical or hemodynamic instabilities that can progress to cardiorespiratory arrest (1,2). The treatment should be immediate, and it is recommended in this clinical condition, to perform reperfusion therapy by primary percutaneous coronary intervention (PCI), In case of non-availability, fibrinolytic therapy should be indicated (1,3) cardiohemodynamic events during rehabilitation will be analyzed. It is expected to observe, at the end of the study, a positive effect of in-hospital CR on cardiac structure and function and its clinical repercussions on the increase of physical fitness, allowing a greater understanding of exercise prescription variables and their physiological responses to predict more therapeutic strategies efficient and early interventions during the in-hospital rehabilitation process in patients with AMI.

The death of cardiomyocytes secondary to the process of inefficient perfusion by the affected coronary arteries can be defined by the term acute myocardial infarction (AMI). Myocardial necrosis can be verified through specific exams, the most recommended being the assessment of high sensitivity cardiac troponin (hs-cTn) which defines AMI with its elevation above the 99th percentile of the reference values (3).

Although there are variations between European countries, cardiac ischemia is responsible for approximately 1.8 million deaths annually (4). The most recent 2021 American Heart Association (AHA) Update shows a prevalence of 49.2% (126.9 million) of cardiovascular disease (including ischemic heart disease) in adults (5). Current studies demonstrate a reduction in acute and long-term mortality after AMI and correlate this fact to the greater use of reperfusion therapy by PCI, despite this fact, mortality after a continuous cardiac ischemic event generates substantial deaths with in-hospital mortality of about 13.6% and 1-year mortality of about 10% (3.5).

## 2.0 Cardiac Rehabilitation (CR)

Mortality after long-term AMI can also be positively influenced by another therapy that should be included in the management of patients with ischemic heart disease: cardiac rehabilitation (CR). CR is recommended with a high level of evidence (A) and a strong class of recommendation (I) based on extensive systematic reviews on the topic and duly recommended by clinical guides (3,6–8). CR promotes a reduction in cardiovascular and all-cause mortality and improves quality of life and functional capacity in this profile of patients (6,7). In a recent review on the subject, Cochrane showed a review of 14,486 patients with coronary disease who participated in CR and showed a significant reduction in cardiovascular mortality and hospitalization when compared to the control group (non-RC participants) (9). Clinical outcomes followed in follow-up studies are primarily associated with attenuation and better control of cardiovascular disease (CVD) risk factors by lifestyle change, including a more physically active lifestyle for individuals (10,11).

Cardiac rehabilitation is defined by World Clinical Guides as a multifaceted intervention process that aims to promote the integral recovery (physical and functional improvement as an anchor of this recovery) of patients affected by acute cardiac events or chronic cardiovascular diseases. The formal CR program should be considered an essential phase for all eligible patients, with only a few cases being recommended only home exercise guidance (9,12–21).

CR programming is traditionally subdivided into stages that obey a temporal, spatial logic and the level of clinical support that the patient needs so that the first offer of CR happens in the hospital phase, which aims at early mobilization and rehabilitation with exercise exercises. low intensity, guidance to the patient about their disease and modifiable risk factors, in addition to strategies for adopting a healthy lifestyle with the aim of providing hospital discharge with the best possible physical and mental condition. After hospital discharge, the patient must proceed to continue the extra-hospital or outpatient phases that occur immediately after discharge and is a prolonged stage that continues the process of increasing physical capacity and comes from maintaining active habits as a lifestyle.

Despite the wide scientific-clinical recommendation, there is still a low number of referrals and participation of patients in formal CR after hospital discharge, which points to a non-pharmacological treatment that is still underused, considering the importance of the relationship between clinical need and control of cardiovascular disease x low procedure cost. Data from the American Heart Association (AHA) update warns that only 24.4% of patients are eligible to participate in CR, with an average of 47 days to start rehabilitation. Furthermore, of those who participated in CR, only 26.9% of patients completed the program. Of these, approximately 93% are patients who underwent early cardiac rehabilitation while still in the hospital. These data show that greater investment is needed in the structuring and viability of cardiac rehabilitation sites for better control of cardiovascular disease. In addition, it also shows the need for continuity between the hospital and outpatient phases in order to optimize a continuum between control of future cardiac events.

In view of the previous findings, an issue that may be quite relevant is the absence of early initiation of the rehabilitation process in the hospital phase, which may be a key point in changing the culture of undervaluing CR both on the part of the team of cardiovascular professionals as well as by the patients themselves. The latest scope review on the subject also found that most of the body of current scientific evidence is based on experimental studies from the pre-PCI revascularization era, which does not reflect the current clinical context, in addition, the clinical guidelines of cardiovascular societies do not provide specific recommendations for the hospital phase of CR (22). Finally, there is a gap in scientific knowledge about the safe time to start CR, its benefits, safety, and prescription parameters in the in-hospital context.

### 3.0 Physical fitness after Cardiac Rehabilitation

The state of sedentary lifestyle is already pointed out in the scientific literature as a risk factor crucial for primary and secondary cardiac events (23). In correlation with this finding, other studies demonstrate the level of cardiorespiratory fitness (CRF), a component of physical fitness, as the greatest predictor of mortality compared to any other cardiovascular risk factor. Therefore, ACR has been evaluated in several studies that seek to verify the benefits of CR, due to its

notorious modification during treatment. Previous work has shown an average gain of 11 to 36% in ACR after traditional outpatient CR, with greater gains in patients who had lower ACR levels at the beginning of the program (24). Thus, there is sufficient evidence to prove that improvements in ACR can explain most of the physical, psychological, and functional benefits, as well as the clinical outcomes of mortality and hospitalization after carrying out a formal CR program (10,25–27).

Among the physiological effects promoted by the physical component of CR that may justify the ACR gains and their repercussions for the general health status after the program are: Attenuation of the severity of ischemia induced by exertion with improvement of angina at rest by raising ischemic thresholds and improvement of endothelial dysfunction, increase in peak oxygen consumption and maximal aerobic power with improvement in skeletal muscle oxidative capacity, reduction in neurohumoral exacerbation, favorable action on the lipid profile, especially in cases of hypertriglyceridemia, decreased levels of HDL-cholesterol and changes in LDL-cholesterol subfractions, hypotensive effect of exercise with reduction of systolic and diastolic pressure levels (9).

In the in-hospital phase of CR, some clinical trials also demonstrated improvement in relation to physical fitness components through indirect or estimated measures of the ACR, such as a significant increase in the distance covered in the six-minute walk test (6MWT) (28, 29). Despite this, many hospital services do not have adequate physical structure to carry out the 6MWT, which requires a flat and continuous corridor of 30 meters and more than one evaluator to perform the test. Other submaximal exercise tests have been used for functional assessment and estimation of physical fitness components. A less expensive possibility in relation to the number of evaluators and physical space is the 30-second sit-to-stand test. The 30s sit-to-stand test has already been validated for the elderly population and patients with Chronic Obstructive Pulmonary Disease (COPD), including established clinically relevant differences for follow-up effects with exercise intervention (30,31). No clinical trials, to date, have evaluated the validity and safety of this functional test with patients hospitalized after AMI.

The assessment of the effects of CR is traditionally verified through direct measurement of the ACR through a cardiopulmonary stress test, obtaining the direct measurement of the peak oxygen consumption ( $VO_2$  peak), a method recommended by several international guidelines (32,33 ). Only one CR hospital-phase clinical trial (29) performed the cardiopulmonary test to

assess peak VO2, 30 days after CR in the profile of patients after coronary artery bypass grafting (CABG). There is, however, a great lack of direct analysis of ACR in post-AMI clinical patients undergoing PCI.

#### 4.0 Heart morphology after cardiac rehabilitation

Despite the well-documented effects of cardiac rehabilitation in patients with AMI with and without heart failure (HF), there is still uncertainty about this effect on ventricular remodeling. Ventricular remodeling is a broad term used to describe genetic, molecular, neurohumoral, cellular, and interstitial alterations that can culminate in changes in the geometry, mass, and function of the ventricle. In AMI, depending on the magnitude, this event can determine the emergence of acute or chronic cardiac dysfunction such as heart failure. The term reverse cardiac remodeling (RCR) has been used to define the partial reversal of this condition as a response to drug treatment, use of implantable resynchronizers, or more uncertainly, aerobic physical exercise, which have brought about improvement in survival and quality of life (34).

Aerobic physical training has still conflicting results in the scientific literature and it is not clear how it can interfere with ventricular remodeling and contribute to reverse ventricular remodeling. Some studies reported attenuation of ventricular remodeling with physical training (35,36), while others worsened the progression of remodeling (37,38) and others, no relation with remodeling (39,40). Despite the divergent results, it is important to pay attention to the start time of cardiac rehabilitation programs that were not uniform in the studies and the clinical severity after AMI, as well as the level of dysfunction that can be verified by the left ventricular ejection fraction (LVEF).

Observing these possible factors interfering with these results, a systematic review with meta-analysis verified the influence of different times of onset of CR in post-AMI patients with reduced LVEF and observed that better changes in ventricular remodeling and cardiorespiratory capacity with early onset of CR, between 6h and 7 days (acute phase) without an increase in adverse events (41). Despite this, the studies included in the previous review addressed continued CR with a broad outpatient phase, thus, to our knowledge, there are no studies evaluating cardiac morphology immediately after the in-hospital phase as a way to assess the effectiveness of this phase of rehabilitation.

## 5.0 Cardiac autonomic function after cardiac rehabilitation

Heart rate variability (HRV) is an easy and non-invasive method to assess the integrity and function of the autonomic nervous system on heart rhythm, in addition to determining risks related to cardiac and non-cardiac diseases (42). HRV has been extensively described after AMI in assessing the prognosis after the event. One of the initial studies describing the relationship between HRV after AMI verified that the reduction of HRV in patients admitted to the critical care unit after AMI increased in-hospital mortality (43). Its prognostic value was later independently confirmed for predicting mortality (44). Despite the great scientific description of its prognostic value, few studies have been directed toward the search for therapeutic effects on HRV. A recent systematic review investigated the effect of physical exercise on HRV after AMI only in the outpatient phase of CR and showed that the results are still divergent, out of eleven clinical trials, five did not show any results on HRV, but six trials showed favorable results. in relation to better autonomic control after exercise-based CR (45). We still do not know the effect of CR on HRV in the in-hospital phase of CR

## 6.0 Cardiac rehabilitation dose and safety aspects

Even with the recognition of the effects and clinical studies of cardiac rehabilitation exercises being dose-dependent, there are important aspects to be considered in terms of dose versus safety in the procedure. The Kanazawa study, 2020, obtained a dose-response trend for in-hospital CR and clinical outcomes such as the risk of revascularization and hospital readmission for all causes, obtaining a significant reduction of these steps in the group of patients who underwent the a from 8 CR sessions during a hospital stay (46). Despite this, no clinical trial located the numerical dose prescribed to patients, matching the prescription parameters and providing a specific targeting of the dose of exercises performed during the in-hospital phase of CR and, therefore, the need to safely guarantee the benefits to be achieved. health. The lack of standardization of dose x cardiac safety in the procedure weakens the adoption of early and safe strategies for maintenance or even the adoption of CR procedures after the cardiac event in an early hospital phase.

Another recent study by Keteyian et al., 2018, retrospectively analyzing a large sample of patients who underwent CR over 5 years, showed important findings. Patients who increased their training workload by 1 MET at the end of CR had a 38% lower adjusted risk and a 42% lower chance of hospitalization and all-cause mortality. This fact points to the need for monitoring the exercise prescription variables during CR as a way to ensure the greatest possible ACR gain for each patient, considering its impact on survival (47). This message should also be incorporated during the initial in-hospital CR prescription.

Numerous evidence therefore demonstrate the potential effect of ACR on clinical outcomes. The increase in ACR and its protective effect is directly related to the dose of aerobic exercise prescribed during CR. The dose of aerobic exercise can be defined as the total energy expended in exercise during a week of training and mathematically described through the analysis of training prescription parameters, such as frequency, intensity, and time. The position on the progression of the exercise dose in CR by the AACVPR (American Association of Cardiovascular and Pulmonary Rehabilitation) together with the ACSM (American College of Sports Medicine) in 2018, demonstrates that the dose value of aerobic exercise between 500-1000 METxmin/week generate a significant reduction in premature mortality and cardiovascular diseases (48).

In view of the findings regarding the theme of the CR results on functional capacity and its impact on the morbidity and mortality of patients, there was a lack of studies that focused on dosing the aerobic exercise prescribed during in-hospital CR and determining the efficacy and safety of this dose. In addition, knowing that the higher the level of cardiorespiratory fitness at the end of CR, the better the survival rate, it is notably important to study the impact of exercise dosage in the search for optimization of CR results, since there are still patients who are little or no responders in relation to ACR gain after the program.

This study becomes necessary, therefore, considering the importance of determining the ideal dose of aerobic training during in-hospital CR in the search for optimizing the results in RCA and its impact on the clinical prognosis of patients compared to the conventional CR process. Serving as a model for calculating the dose of aerobic training that is easy to include in the clinical routine of in-hospital CR sectors. It is also important to verify the cardiac morphological and functional repercussions of early CR, as well as the clinical impact of this change on the physical and functional aspects of the patient. Finally, it will establish the level of cardiohemodynamic

safety of this therapy in an early phase.

Thus, the general objective of this study will be to describe the dose of aerobic exercise offered during early CR and its effect on physical fitness, morphology cardiac function, and safety aspects in patients after AMI.

## **STUDY OBJECTIVES**

### **Primary objective**

To evaluate the efficacy and safety of early CR after AMI and its effect on physical fitness, morphology, and cardiac function.

### **Secondary objectives**

- To assess the variation in functional capacity by measuring cardiorespiratory fitness after in-hospital CR, using maximum VO2 (maximum oxygen consumption) as a result measure;
- To analyze the dose of aerobic training provided to patients in in-hospital CR and its impact on the outcome of functional capacity;
- Relate the standard method of measuring VO2, the cardiopulmonary test, to a submaximal evaluation method, the 30s sit-to-stand test, evaluating its validity and reproducibility;
- Observe the influence of early CR on the morphological parameters of ventricular remodeling through nuclear magnetic resonance (NMR);
- Investigate heart rate variability after early cardiac rehabilitation.
- Identify the rate of adverse events and the safety level of the protocol evaluated in this clinical trial;

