## **Sampling and Recruitment**

Participants will be recruited from the adult intensive care unit (ICU) shortly after admission for a percutaneous coronary intervention (PCI) procedure. The sample size was calculated using the OpenEpi software through the mean difference found in a previous study (29) with in-hospital CR for analysis of maximum oxygen consumption (VO2). A number of 7 participants per group was verified with a total of 14 for the sample considering a significance level of 5%, and a statistical power of 80%. Adding a 30% rate for possible losses during the study, we chose to recruit 12 participants per group for a total sample size of 24 patients. The patients included in the study will be patients admitted to the adult ICU at HUOL with a confirmed clinical diagnosis of AMI (ECG and cardiac enzymes) with or without ST elevation and uncomplicated (Killip I or II), undergoing percutaneous coronary intervention (PCI) with success (Timi flow 2 or 3), aged between 18 years and 70 years and of both sexes, classified as low risk (EF>50%, absence of ventricular dysrhythmias, absence of clinical depression and ischemic signs or symptoms after the procedure) according to the American Association of Cardiovascular and Pulmonary Rehabilitation (AACPR) risk classification (50) and ability to provide informed consent. Exclusion criteria determined include the presence of musculoskeletal disorders that prevent the performance of exercises, signs, and symptoms of cardiac ischemia or decompensation, atrial or ventricular arrhythmias, and diagnosed pulmonary diseases (e.g., pulmonary hypertension, COPD, among others).

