### Cardiohemodinamic safety of early cardiac rehabilitation

The safety of the institutional protocol tested in this trial will occur through notifications

of adverse events during and after the CR sessions provided to patients in the intervention group. We will report adverse events session by session, listing the main ones: arrhythmias, chest pain, borg>13, drop in systolic blood pressure (SBP) above 10 mmHg, and cardiorespiratory arrest. Other events not previously listed will also be recorded in the patient follow-up and evaluation form as per Appendix A.

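### Safety is part of the primary objective, but session-by-session event reporting in 12 treated patients cannot exclude a per-patient risk of about 26% for a rare serious event

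*Protocol*

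**What the plan says.** Safety appears at three levels of ambition in the Protocol. The primary objective is "To evaluate the efficacy and safety of early CR after AMI", together with its effect on fitness, morphology and cardiac function. The secondary objectives add an aim to "Identify the rate of adverse events and the safety level of the protocol evaluated in this clinical trial". The Introduction (6.0, on dose and safety aspects) says of the study: "Finally, it will establish the level of cardiohemodynamic" safety of the therapy.

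The method is in the section on cardiohemodynamic safety. It relies on notification "of adverse events during and after the CR sessions provided to patients in the intervention group", and states: "We will report adverse events session by session, listing the main ones". The listed types are arrhythmia, chest pain, Borg above 13, a systolic pressure drop above 10 mmHg and cardiorespiratory arrest.

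The size of that group is in Sampling and Recruitment: "we chose to recruit 12 participants per group for a total sample size of 24 patients". The calculation rests on a mean difference in maximum oxygen consumption. The Statistic Strategy section covers the sit-to-stand test, MRI, heart rate variability, the cardiopulmonary test and reliability, and does not mention adverse events.

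**The concern.** The objectives promise a rate and a level of safety. The method supplies a list of events by session from 12 people. For frequent minor events, such as a high Borg score, that list will be informative. For rare serious events the most likely result is none or one, and the Protocol does not say how much risk such a result leaves open.

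The choice of unit matters too. At the average of 8 to 10 sessions per patient given in the rehabilitation programme section, 12 patients contribute roughly 96 to 120 sessions. A rate with sessions in the denominator looks small and precise, yet the information about a patient's risk comes from 12 people. At stake is whether the safety statement attached to the primary objective reflects what the data can exclude.

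**Working it through.** **Inputs.** Intervention group n = 12 (Sampling and Recruitment). Sessions per patient: 8 to 10 on average (Early cardiac rehabilitation program). Tolerable event rate: none stated, so the risks in step 3 are illustrative assumptions.

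**1. The plan's own figure.** The Protocol gives 7 per group at 5% significance and 80% power, then 12 after an allowance for 30% losses. The oxygen-consumption difference and standard deviation are not given, so the 7 cannot be reproduced. By the normal approximation (two-sided) it implies a standardised difference of √(2/7) × (1.96 + 0.84) ≈ 1.5. Inflating 7 for 30% losses gives 7 / 0.7 = 10; the text says 12 was chosen. The safety point needs only the 12.

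**2. What zero events in 12 patients exclude.** The exact (Clopper-Pearson) upper limit for 0 of n is 1 − a^(1/n).
- Two-sided 95%: 1 − 0.025^(1/12) = 26.5%.
- One-sided 95%: 1 − 0.05^(1/12) = 22.1%.
- Rule of three as a check: 3/12 = 25%.

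If one patient in 12 has the event, the exact two-sided interval runs from 0.2% to 38.5%.

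**3. How often a real risk would go unseen.** The probability of no affected patient among 12 is (1 − p)^12.

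| Assumed per-patient risk | Chance of 0 of 12 |
|---|---|
| 5% | 54% |
| 10% | 28% |
| 20% | 7% |

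**4. Why the unit matters.** Suppose, for illustration only, that zero events were set against sessions treated as independent. The two-sided limit would be 1 − 0.025^(1/96) = 3.8% for 96 sessions and 1 − 0.025^(1/120) = 3.0% for 120. Sessions within a patient are correlated. With m sessions per patient and intraclass correlation ρ, the effective number is 12m / (1 + (m − 1)ρ). For m = 8, with ρ unknown and therefore varied:

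| ρ (assumed) | Effective number | Two-sided upper limit |
|---|---|---|
| 0 | 96 | 3.8% |
| 0.2 | 40.0 | 8.8% |
| 0.5 | 21.3 | 15.9% |
| 1 | 12 | 26.5% |

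A risk per session and a risk per patient are also different quantities. The patient-level limit needs no assumption about ρ.

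**The case against.** The strongest reply is that the Protocol never says a record without events means the treatment is safe. That is correct. A reader might infer such a rule from the promise to establish a level of safety, but no passage states it. The wording can also mean measuring the level, and the sentence that follows it in the Introduction gives the general aim as describing dose, effect and safety aspects. Nor does the Protocol plan an interval that treats sessions as independent; step 4 shows only what a per-session rate could suggest.

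Other parts of the reply also stand:

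- A wholly clean record is unlikely, because a Borg score above 13 and a modest pressure drop count as events. The zero-event limit therefore applies to rare serious types, taken one at a time.
- A reader might shrink the denominator by the 30% loss allowance. The documents do not support this. The allowance belongs to the oxygen-consumption sample, measured at reassessment from 30 days after discharge. In-hospital session records already exist when that visit is missed.
- Session listing is not the only safety information. The abstract mentions safety scores, vital signs are recorded each session, and the Appendix A form has an adverse-event field for each sit-to-stand test, which both groups perform.
- Exact intervals and the unit of analysis are often left to a statistical analysis plan, which is not at hand. Their absence from the Protocol is not in itself a fault.

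What the reply does not remove is the mismatch between the stated aim and the stated method. No analysis plan can change what 12 patients can exclude, and the Protocol itself names the session as the reporting unit.

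**Conclusion.** The point holds as a mismatch between aim and design. For a rare serious event type, no events in 12 intervention patients leaves a per-patient risk of up to 26.5% (two-sided exact 95%; 22.1% one-sided) compatible with the data. An illustrative true risk of 10% would go unseen in 28% of such trials. These figures assume that all 12 patients are exposed and that patients are independent with a common risk.

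The trial's efficacy comparison is unaffected, and a small trial may reasonably describe safety. It cannot establish a level of safety for rare serious events, and a rate per session would hide that limit. It would go too far to say that the Protocol treats absence of events as proof of safety: that reading is only an inference. The change is a worthwhile, inexpensive improvement.

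**What to change.** 1. In the cardiohemodynamic safety and Statistic Strategy sections, make the patient the unit. For each listed event type, report the number of patients with at least one event over the number exposed, with an exact (Clopper-Pearson) 95% interval. Keep the session-by-session listing as description.
2. In the Introduction and the secondary objectives, replace the promises to establish, or identify, a level of safety with an aim to describe adverse events and the highest event risk compatible with the data.
3. Before counting, reconcile the event definitions. The safety section uses Borg above 13 and a systolic drop above 10 mmHg; the session form in Appendix A uses 13 or more and 10 mmHg or more. A session at exactly 13 or exactly 10 mmHg is an event on the form and not in the text.

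The cost is some rewording and one interval per event type, from records the form already collects. No further patients or measurements are needed. The downside is a less favourable safety claim.
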